### Ethical Considerations

This study has been approved by the medical ethics committee of the Amsterdam University Medical Centers (file number 2020_154 - NL74494.018.20). The trial has been registered at ClinicalTrials.gov (number NCT05093036).

## Results

The results of the primary outcome assessment are expected by Fall 2024. Completion of the 24-month questionnaire and retrieval of STI data are expected by Fall 2024. Analysis of secondary outcomes will be conducted in 2024 and 2025.

## Discussion

We have designed the EZI-PrEP study in order to assess whether online-mediated PrEP care and a reduced frequency of monitoring are noninferior compared to standard practice. In this study, we will develop, implement, and rigorously evaluate an online-mediated PrEP care service and a less frequent monitoring schedule (every 6 months) among MSM and TGDP in 4 regions in the Netherlands. Studies in countries with concentrated HIV epidemics and PrEP programs for MSM show the potential of PrEP programs to reduce population-level HIV incidence [57,58]. Reducing the number of in-clinic visits may reduce the burden of PrEP care and might help increase uptake and improve retention. Additionally, it may improve access to PrEP as it may make more resources available and enlarge capacity at facilities providing PrEP. Online-mediated PrEP care and monitoring every 6 months are promising options to reduce in-clinic PrEP visits, but it is unclear how this affects PrEP adherence. Since both modalities involve less intense contact between PrEP users and health care providers, and thus less guidance in PrEP use, it could theoretically have an adverse effect on PrEP adherence. The EZI-PrEP study will be able to provide evidence on the efficacy and safety of online-mediated PrEP care and PrEP care every 6 months compared to standard in-clinic PrEP care every 3 months in terms of PrEP adherence as a proxy for HIV risk. If these services are found to be noninferior, both online access to PrEP and reduced monitoring frequency could become viable evidence-based PrEP care options.

The EZI-PrEP study will contribute crucial data to the ongoing debate on optimal HIV and STI screening frequency for MSM who use PrEP. By comparing incidence rates of HIV infection, STIs, and HCV infection between the 3-month and 6-month monitoring study arms, we will provide evidence on the impact of testing every 6 months on STI diagnosis and treatment. If noninferiority in terms of PrEP adherence is concluded and STI incidence rates are similar between the 6-month and 3-month monitoring arms, a stronger case can be made to offer PrEP monitoring every 6 months as the standard of care. If STI incidence rates are not similar between the study arms, we will be able to examine to what extent this is related to particular sociodemographic, sexual behavior, or psychosocial factors and advise on implementation accordingly. EZI-PrEP study participants will be allowed to test for HIV, STIs, and HCV in between regular PrEP monitoring visits at their own initiative. The EZI-PrEP study will also be able to quantify the extent to which in-between visits occur among PrEP users receiving monitoring every 6 months.

Since adherence to the PrEP intake regimen is crucial for its effectiveness [3,5-7], having a thorough understanding of enabling and disenabling factors of PrEP adherence is important. The EZI-PrEP study will provide new insights on the associations between sociodemographic and psychosocial variables on the one hand and PrEP adherence on the other hand. Insights into the role of such sociodemographic and psychological factors in the context of adherence may be used to further improve the content or conduct of PrEP consultations and inform interventions that support PrEP adherence. Furthermore, we will investigate the relationship of these factors with PrEP adherence, STIs, retention, and satisfaction with PrEP care, according to the study arm. The results of these analyses could be used to determine if these new PrEP care modalities should be implemented widely or should be offered to specific subpopulations.

The main methodological challenge of this study is the measurement of the primary outcome measure, which is based on self-reported PrEP intake and sexual behavior. In the AMPrEP study, it was found that reporting of daily data decreases over time, which may confront us with a substantial amount of missing data. We will therefore implement an intensive scheme of reminders. Additionally, the diary in itself may cause behavioral changes (ie, Hawthorne effect). For instance, PrEP intake may be affected due to the daily reminder to complete the diary. Completing the diary on a daily basis might also be too burdensome for some participants, and as a result, their motivation to complete the study could be low. However, because of randomization, any effect of daily diary entry on behavior or participation is not expected to differ across the 4 arms. A major strength of our study is that it is embedded in routine PrEP care, which increases the generalizability of study outcomes and will provide a realistic perspective on the implementation of 2 new PrEP care modalities. If these modalities are found to be noninferior, they can be easily implemented in routine care using the workflows developed in this study and applied to the 4 participating PHSs. Furthermore, combining monitoring every 6 months and online-mediated PrEP care in this trial offers a unique opportunity to study real-life implementation of these PrEP modalities.

In conclusion, the results of the EZI-PrEP trial will provide evidence on the noninferiority of online-mediated PrEP care compared to in-clinic care and the noninferiority of monitoring every 6 months compared to monitoring every 3 months in terms of PrEP adherence. It will also provide insights into screening every 6 months for HIV infection, STIs, and HCV infection among MSM who use PrEP, and thereby will contribute to the literature on the optimal STI screening frequency among PrEP users. Moreover, the study will investigate to what extent these PrEP care modalities are appealing to PrEP users in general and if particular PrEP users would benefit more from these modalities than others. Finally, the study will provide insights into the sociodemographic and psychosocial factors that influence PrEP adherence. The EZI-PrEP study aims to inform policymakers and sexual health centers in deciding which strategies would be appropriate for PrEP care. The findings will contribute to accessible, low-cost, scalable, and sustainable PrEP care.

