**Conclusions:**

This trial will demonstrate whether online PrEP care and monitoring every 6 months is noninferior to standard PrEP care in terms of PrEP adherence. If noninferiority is established, these modalities may lower barriers for initiating and continuing PrEP use and potentially reduce the systemic burden for PrEP providers.

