### Study Design

The EZI-PrEP study will be a 2×2 factorial, 4-arm, open-label, multi-center, randomized, controlled, noninferiority trial. Study participants will be randomized to 1 of 4 arms: (1) in-clinic monitoring every 3 months (standard of care), (2) in-clinic monitoring every 6 months, (3) online monitoring every 3 months, or (4) online monitoring every 6 months (Figure 1). The study will be implemented at SHCs in Amsterdam, Rotterdam-Rijnmond, Haaglanden, and Gelderland-Zuid (Figure 2). For each individual participant, the planned observation time is 24 months, starting after eligibility screening and enrollment.

All study participants will receive access to a smartphone app (the “EZI-PrEP app”), which contains a diary. Participants will be required to complete this diary daily during the first 18 months of the study period. This information will be used to measure the primary outcome (ie, unprotected acts). DBSs will be collected at months 6 and 12. Routine clinical data registered during PrEP monitoring visits and any additional STI testing or treatment visits from inclusion until the final monitoring visit at month 24 will be retrieved from the national STI surveillance system. Participants will be requested to complete 5 questionnaires (at baseline and at 6, 12, 18, and 24 months) to collect data on PrEP intake; sexual behavior; psychosocial characteristics; and the experiences, acceptability, and usability of the interventions. We will extract automatically registered data on app usage from the app.

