### Randomization

Participants will be randomized (stratified by PHS and by PrEP experience, that is, those starting or restarting PrEP, and current PrEP users) to 1 of 4 study arms in permuted blocks of 4. Randomization will be performed by a statistician of PHS Amsterdam who is not part of the EZI-PrEP study team at initiation of the study, using Stata Intercooled 15.1 (StataCorp). Sequentially numbered and colored nontransparent envelopes will be made, containing a code for the study arm. Each PHS will receive 2 sets of envelopes, red ones for those starting or restarting PrEP and blue ones for current PrEP users. During the enrollment interview, in the presence of the participant and dependent on their PrEP experience, the health care provider will open the next envelope to reveal the study arm and study number.

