### Data Analysis

#### Primary Outcome

The primary outcome (“unprotected act”) will be assessed using daily self-reported data on sexual behavior, pill intake, and condom use. We will use all available data, meaning that observation time and all data of those who are lost to follow-up or have dropped out will be included until their last day in the study. We will determine, for each day of follow-up, whether a condomless anal sex act with a casual partner took place. We will also determine whether sufficient PrEP pills were taken around the time of this condomless anal sex act. Using this information, the condomless anal sex act will be considered as either unprotected or not. We will then calculate the total number of unprotected acts (n) and the total person-years of observation. Incidence rates per 100 person years will be calculated by dividing the sum of all unprotected acts by the sum of person-years of observation and multiplying the result by 100. We will calculate the incidence rates among participants of online PrEP care (arms 3 and 4), in-clinic PrEP care (arms 1 and 2), monitoring every 6 months (arms 2 and 4), and monitoring every 3 months (arms 1 and 3). Two main analyses will be conducted in which we will test the ratio of the incidence rates of unprotected acts for (1) online PrEP care versus in-clinic PrEP care and (2) monitoring every 6 months versus monitoring every 3 months. The analyses will be based on crude unadjusted incidence rate ratios.

A noninferiority trial intends to demonstrate that one intervention is not unacceptably worse than a comparison intervention [54]. To do so, the lower limit of the 95% CI (or 2-sided 97.5% CI) should not extend beyond a predefined margin, which is referred to as the noninferiority margin. In this study, noninferiority will be tested using a 1-sided test based on maximum likelihood estimators with a type 1 error at 0.0125 (ie, with 2 comparisons using Bonferroni corrections=0.025/2) [40] and a noninferiority ratio of 1.8. If the upper 2-sided 97.5% CI of the incidence rate ratio is below 1.8, we will conclude that the intervention arms are noninferior to the comparator arms.

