To determine whether the incidence rates change over time, we will model the number of unprotected acts as a function of 1-month intervals using Poisson regression (or negative-binomial regression, if the standard deviation is far greater than the mean of the outcome, ie, overdispersion) and test for changes in time using a Wald χ^2^ test. We will test for the interaction between time and intervention arm.

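### The stated conclusion is against standard in-clinic 3-monthly care (arm 1), but both primary tests use pooled comparators, so two passes do not show that online 6-monthly care is noninferior to arm 1

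*Protocol article*

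**What the plan says.** All references are to the protocol article.

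- **Study Design** describes a "2×2 factorial, 4-arm, open-label, multi-center, randomized, controlled, noninferiority trial". Arm 1 is "in-clinic monitoring every 3 months (standard of care"), and no other arm carries that label.
- **Randomization** allocates "to 1 of 4 study arms in permuted blocks of 4", so the arms are of equal size.
- **Data Analysis, Primary Outcome** forms its groups from "participants of online PrEP care (arms 3 and 4), in-clinic PrEP care (arms 1 and 2), monitoring every 6 months (arms 2 and 4"); the fourth group, for 3-monthly monitoring, pools arms 1 and 3. The two main analyses are crude rate ratios, online v in-clinic and 6-monthly v 3-monthly. Each is noninferior if the upper limit of the two-sided 97.5% CI is below 1.8. The later paragraph on time trends adds: "We will test for the interaction between time and intervention arm".
- **Abstract, Conclusions** says the trial will show "whether online PrEP care and monitoring every 6 months is noninferior to standard PrEP care".
- **Discussion** (first paragraph) says the evidence on both modalities is "compared to standard in-clinic PrEP care every 3 months in terms of PrEP adherence as a proxy for HIV risk".

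The article describes no contrast on the primary outcome in which arm 1 alone is the comparator.

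**The concern.** The two sentences on what the trial will show name a comparator that neither main analysis uses. In the online v in-clinic test, half of the comparator group is in-clinic 6-monthly care (arm 2). In the 6- v 3-monthly test, half is online 3-monthly care (arm 3). A pooled ratio describes a factor averaged over the two levels of the other factor. It is not a ratio against standard care.

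The difference matters most for arm 4. The Discussion itself says that both modalities mean less contact with providers and could therefore harm adherence. Arm 4 receives both reductions. Each factor can lie within the margin on average while the combination lies at or beyond it against arm 1. A policymaker who reads two positive results under the present wording has no text that warns against applying them to the combination.

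**Working it through.** **Inputs** (Power and Sample Size Calculation; Data Analysis, Primary Outcome): Poisson counts; 0.36 unprotected acts per person-year; 1.5 years of monitoring; margin 1.8; one-sided error 0.0125 (z = 2.2414); 368 evaluable participants, or 442 after adding 20%. Equal arms give 92 or 110.5 per arm.

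**The plan's own figure.** 368 × 1.2 = 441.6, which rounds to 442 and agrees. The 368 itself does not follow from the stated inputs by the formulas tried. The Wald test on the log ratio gives 268, the linear statistic with restricted ML variance 276, the square-root transform 276, and the linear statistic with unrestricted variance 306. The stated number is on the large side, and this point does not depend on it. Results below are shown for both 368 and 442.

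**Check with no true difference.** Events per pooled group are 184 × 0.54 = 99.4 or 221 × 0.54 = 119.3. Power = Φ(ln 1.8 / √(2/events) − 2.2414) = 97% or 99% for each pooled test.

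**True arm 4 v arm 1 ratio set at 1.8, two patterns of harm**

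Each pooled test passes with probability Φ(ln(1.8/R)/SE − 2.2414), where R is the true pooled ratio and SE = √(1/E + 1/C). E and C are the expected events in the experimental and comparator groups.

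*(a) Only arm 4 is harmed.* R = (1 + 1.8)/(1 + 1) = 1.40.
- N 368: C = 99.4, E = 139.1, SE = 0.131; Φ(0.2513/0.131 − 2.2414) = 0.37.
- N 442: C = 119.3, E = 167.1, SE = 0.120; result 0.44.

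*(b) Multiplicative harm, no interaction.* Each factor has ratio √1.8 = 1.34, so R = 1.34.
- N 368: C = 99.4 × (1 + 1.34)/2 = 116.3, E = 156.1, SE = 0.122; Φ(0.2939/0.122 − 2.2414) = 0.56.
- N 442: C = 139.7, E = 187.5, SE = 0.112; result 0.65.

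The chance that both pooled tests pass comes from simulating four Poisson arms with Wald 97.5% CIs:

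| True pattern (arm 4 v arm 1 = 1.8) | Each pooled test passes | Both pass | Direct arm 4 v arm 1 passes | 5% interaction test rejects |
|---|---|---|---|---|
| (a) harm only in arm 4 | 37–44% | 16–22% | about 1.3% | 59–68% |
| (b) multiplicative | 56–65% | 31–42% | about 1.3% | 5% (nothing to find) |

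Ranges run from N 368 to N 442.

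**What a direct contrast can show.** Expected events per arm are 92 × 0.54 = 49.7 or 110.5 × 0.54 = 59.7. SE = √(2/49.7) = 0.201 or √(2/59.7) = 0.183. With no true difference, power is Φ(0.5878/0.201 − 2.2414) = 75%, or 83% at N 442. The interval lies below 1.8 if the observed ratio is below 1.8 × exp(−2.2414 × 0.201) = 1.15, or 1.19 at N 442.

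**The case against.** The strongest defence is that the plan is consistent where it counts. The objectives, the two main analyses and the final paragraph of the Discussion all state the two marginal comparisons. The trial was sized for them, and pooled comparisons are what a factorial design is for. This stands: the primary tests are not wrong and need not change.

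Three stronger readings are tempting, and the documents do not support them.

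- *The trial will endorse online 6-monthly care.* A reader might infer this from the Discussion, which calls the modalities easy to implement if noninferior and welcomes the chance to study their combination. No sentence declares arm 4 noninferior to arm 1, and no decision rule is set for it.
- *The missing modality-by-frequency interaction test is the defect.* The article names only a time-by-arm interaction. A factor interaction may well be in an analysis plan that is not shown. Such a test also would not cure the problem: in pattern (b) it has nothing to detect, and in pattern (a) it detects the harm in only 59–68% of trials.
- *Two passes could hide a ratio of 1.8 × 1.8 = 3.24.* That is an arithmetical bound. With both true ratios at 1.8, each test passes in about 1.25% of trials, and both pass in about 0.0125 × 0.0125, or 0.02%.

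It is also fair to say that a formal noninferiority requirement for arm 4, at 75–83% power, would be a new design choice and not the correction of an error. What remains is the mismatch in two sentences, and the absence in the article of any estimate against arm 1.

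**Conclusion.** The point holds as a mismatch between the stated conclusion and the tested contrasts. The Abstract and Discussion claim a comparison with standard care. The analysis compares pooled groups, each comparator being half non-standard care. If online 6-monthly care is truly at the margin of 1.8 against arm 1, both pooled tests still succeed in 16–22% of trials (harm confined to arm 4) or 31–42% (multiplicative harm), against about 1.3% for a direct comparison. Two pooled passes are therefore not evidence that the combination is noninferior to standard care.

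The figures assume pure Poisson counts, equal arms, 0.36 acts per person-year in arm 1 and 18 months of monitoring for all. Overdispersion, which the plan allows for in its time-trend model, would change the percentages but not the mismatch. The two patterns of harm are illustrations; the documents do not predict either.

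**What to change.** 1. Reword the Abstract conclusion and the Discussion sentence so that they claim only the two comparisons tested: online v in-clinic care, and 6-monthly v 3-monthly monitoring, each averaged over the other factor.
2. Under Primary Outcome, add the four arm-specific rates and the rate ratios of arms 2, 3 and 4 v arm 1, with 97.5% CIs read against 1.8. Report the modality-by-frequency ratio of rate ratios with its CI as supportive only.
3. State that two pooled passes do not by themselves establish noninferiority of online 6-monthly care to standard care, and that any such claim rests on the arm 4 v arm 1 interval.

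The primary tests, error rate and sample size stay as they are. The cost is a few lines of text and one table. The downside is that arm-level intervals are wider. Power for arm 4 v arm 1 is about 75–83% with no true difference, and lower with overdispersion, so a claim for the combination becomes harder to make.

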## Appendix

Multimedia Appendix 1 Laboratory procedures at each study site.

## Abbreviations

AMPrEP: Amsterdam PrEP demonstration project
DBS: dried blood spot
eGFR: estimated glomerular filtration rate
EZI-PrEP: E-Health for Zero Infections - facilitating access to and use of Pre-Exposure Prophylaxis in the Netherlands
FTC: emtricitabine
FTC-TP: emtricitabine-triphosphate
HCV: hepatitis C virus
MSM: men who have sex with men
NPP: National PrEP Pilot Program
PHS: public health service
PrEP: pre-exposure prophylaxis
SHC: sexual health center
STI: sexually transmitted infection
TFV: tenofovir
TFV-DP: tenofovir-diphosphate
TGDP: transgender and gender diverse people
